**Figure 5. F5:**
[figure not shown]
Demonstration of artificial intelligence (AI)–assisted screening for diabetic retinopathy (DR; A and B) and age-related macular degeneration (AMD; C and D).

For DR screening, the AI system outputs the original color fundus image (panel A), a referral recommendation (positive or negative), DR severity grading (0: no DR; 1: mild nonproliferative diabetic retinopathy [NPDR]; 2: moderate NPDR; 3: severe NPDR; and 4: proliferative diabetic retinopathy [PDR]), image quality assessment (good or bad), and automated lesion annotation with lesion counts (panel B). As shown on the right, annotated lesions include hemorrhages (green), hard exudates (blue), and microaneurysms (yellow).

For AMD screening, the AI system provides the original color fundus image (panel C), a referral recommendation (positive or negative), AMD severity grading (AMD level <3 or AMD level ≥3), image quality assessment (good or bad), and corresponding red-free image (panel D) to enhance the contrast of specific retinal structures and lesions.

### Treatment

For DR, management depends on both DR severity and the presence of diabetic macular edema (DME). Mild to moderate NPDR without vision-threatening DME is typically monitored with periodic follow-up, usually every 6 to 12 months, depending on the risk. As the disease progresses to severe NPDR, closer monitoring is generally advised, and anti–vascular endothelial growth factor (anti-VEGF) therapy may be considered for selected patients. Once the disease progresses to PDR, prompt treatment is essential. While pan-retinal photocoagulation remains a standard treatment for PDR, intravitreal anti-VEGF injections have also become an alternative, offering visual benefits with less peripheral field loss. Anti-VEGF therapy is the first choice for center-involved DME with visual impairment, and DME can occur at any stage of DR. In PDR complicated by nonclearing vitreous hemorrhage and/or macula-threatening tractional retinal detachment, pars plana vitrectomy is often indicated. Managing AMD is similar to that of DR, with treatment strategies tailored to the disease stage. Early AMD focuses on modifying risk factors and regular monitoring. For intermediate AMD, antioxidant vitamins and minerals based on the AREDS2 formula, which replaces β-carotene with lutein and zeaxanthin, should be considered to lower the risk of progression [27]. In advanced AMD, especially the neovascular type, intravitreal anti-VEGF therapy is the standard treatment. These agents inhibit choroidal neovascularization, decrease exudation and retinal fluid, and often help stabilize or enhance visual acuity [28].

### Outcome Measures

All participants in both the intervention and control groups will undergo follow-up assessments and review of medical records to evaluate the outcomes of DR and AMD. The primary, secondary, and subsidiary outcomes are shown below.

#### Primary Outcome

The primary outcomes are the detection rate and PPV of DR and AMD screening.

Detection rate:

$$\frac{Number\;of\;people\;with\;the\;confirmatory\;diagnosis\;of\;AMD\;or\;DR}{Number\;of\;people\;who\;participate\;in\;screening}$$

PPV:

$$\frac{Number\;of\;cases\;the\;confirmatory\;diagnosis\;of\;AMD\;or\;DR}{Number\;of\;screened\;positive\;cases}$$

Detection rate is defined as the proportion of screened participants who receive a confirmatory diagnosis of DR or AMD among all participants who undergo screening. PPV is defined as the proportion of participants with a confirmatory diagnosis among those who test positive in the screening.

The intention-to-screen population will include all randomized participants, who will be analyzed according to their assigned group regardless of adherence to the screening or referral process. Missing outcome data, particularly those resulting from incomplete referral follow-up, will be addressed under the intention-to-screen principle and reflected in the detection rate. Specifically, participants who test positive but are not referred for confirmatory diagnosis will remain included in the denominator when calculating detection rates, although they will not contribute to the numerator. The per-protocol population will include participants who complete the screening and adhere to the predefined study procedures. Participants with incomplete referral follow-up who test positive but do not comply with referral for confirmatory diagnosis will be excluded from both the numerator and denominator when calculating the PPV.

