**Results:**

The study was funded in September 2024, began on October 2, 2025, and is expected to be completed in December 2027. After the pilot implementation phase without randomization, participants will be randomized 1:1 into two groups: (1) AI-assisted screening, and (2) usual physician-only screening. The primary outcomes will include the detection rates (defined as participants with confirmed DR or AMD among all screened participants) and the positive predictive values (defined as participants with confirmed DR or AMD among those who tested positive). Cost-effectiveness analyses will be performed using data derived from the trial results.

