### Inclusion and Exclusion Criteria

Inclusion criteria include adults aged ≥20 years with diabetes undergoing screening for DR and adults aged ≥50 years undergoing screening for AMD. Potential participants will be identified during routine clinic visits, and eligible individuals who express interest will receive detailed study information. Written informed consent will be obtained prior to enrollment. Participants will be excluded if they decline participation or are unable to provide informed consent because of cognitive or communication limitations.

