### Randomization

Participants will be randomized at the individual level in a 1:1 ratio to either the AI-assisted screening group or the conventional physician-based screening group. Randomization is performed on a per-participant basis, and sample size estimation will be based on this process. DR and AMD are managed within a single unified cohort. DR and AMD can be diagnosed in the same patient, while DR and AMD are treated as separate disease-specific outcomes, and analyses will be conducted independently for each condition based on predefined eligibility criteria. Participants eligible for both conditions may contribute to both analyses.

In the conventional physician-based screening arm, fundus photographs will be interpreted by physicians without the use of any AI assistance. Physicians will review the images independently based on their clinical judgment. All physicians involved in image interpretation will receive standardized training in fundus photograph assessment prior to study initiation. In addition, a standardized reading guide will be provided to ensure consistency in image interpretation across the control group.

Randomization will be conducted using a computerized randomization module embedded within the rule engine of AIMIGS. After enrollment, each participant will be assigned a unique study ID, and allocation will be automatically generated by AIMIGS. Once the assignment is generated, the system automatically allocates each participant to the designated study arm and triggers the corresponding imaging procedures according to the predefined workflow.

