### Sample Size Estimation

The estimated prevalence of any DR (across stages 1-4) and AMD is 27% and 10%, respectively [29,30]. For this study, the sample size is calculated based on the assumption that 10% of patients with diabetes aged ≥20 years are diagnosed with clinically significant DR (stages 2 to 4) in the Department of Family Medicine and the Department of Geriatrics and Gerontology. Using AI-assisted diagnostic tools, the detection is assumed to increase to 15% [31].

In this real-world pragmatic setting, there was no prior evidence on the referral rates for eye disease screening in Taiwan. This study therefore assumed a referral rate of approximately 70% based on large-scale pragmatic screening trials of fecal occult blood testing and *Helicobacter pylori* stool antigen testing in Taiwan [20,21]. Accordingly, it is assumed that 70% of screen-positive individuals will be successfully referred to ophthalmologists for further examination and with a 2-tailed test, a type I error (α) of .05, and a type II error (β) of .10, the required sample size is 2612 participants (1306 per group). Approximately 870 participants are expected to be enrolled annually over an anticipated 3-year study period.

For patients aged ≥50 years in the Department of Family Medicine and the Department of Geriatrics and Gerontology in the NTUH, the prevalence of AMD is 5%, which is assumed to increase to 10% with the use of AI-assisted diagnostic tools. Assuming that 70% of the screening cases can be successfully referred to ophthalmologists and with a 2-tailed test, a type I error (α) of .05, and a type II error (β) of .10, the required sample size is 1650 participants (825 per group). Approximately 550 participants are expected to be enrolled per year.

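### The primary-outcome definition pools DR or AMD over everyone screened, but the analysis rule and the sample sizes are disease-specific; the definition should be aligned with them.

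*Protocol article*

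**What the plan says.** All places are in the protocol article.

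- **Primary Outcome.** The formula counts people with a confirmatory diagnosis of AMD or DR over people who take part in screening. The prose agrees: "Detection rate is defined as the proportion of screened participants who receive a confirmatory diagnosis of DR or AMD among all participants who undergo screening". The PPV formula has the same two-disease numerator over all screen-positive cases. The PPV prose names no disease.
- **Abstract, Results.** The detection rate is "defined as participants with confirmed DR or AMD among all screened participants" and the PPV is "defined as participants with confirmed DR or AMD among those who tested positive".
- **Inclusion and Exclusion Criteria.** Two populations are eligible: "adults aged ≥20 years with diabetes undergoing screening for DR and adults aged ≥50 years undergoing screening for AMD".
- **Randomization.** DR and AMD are managed in one unified cohort, yet "DR and AMD are treated as separate disease-specific outcomes, and analyses will be conducted independently for each condition based on predefined eligibility criteria". Further, "Participants eligible for both conditions may contribute to both analyses".
- **Sample Size Estimation.** DR is sized on 10% vs 15% (1306 per group). AMD is sized on 5% vs 10%: "the required sample size is 1650 participants (825 per group"). No size is given for a combined rate.
- **Statistical Analysis.** Two-sample proportion tests are planned for the detection rates and the PPVs, without saying whether these are per disease or combined.

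**The concern.** The cohort is unified, so a numerator of DR or AMD over all participants is, taken literally, one pooled outcome across people with diabetes and people aged 50 or over. That is not what the Randomization section analyses or what Sample Size Estimation powers. The definitions differ in the numerator (either disease or a named one) and in the denominator (everyone or those eligible).

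Three things are at stake.

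- A pooled rate can hide an effect on one disease, or lend one disease's effect to the other. The intervention is two software products with separately reported accuracy, so unequal performance is plausible.
- Under the pooled PPV formula, a participant flagged for one disease and confirmed with only the other counts as a true positive.
- The cost-effectiveness section builds separate DR and AMD models that take detection rates from the trial. A pooled rate cannot feed either one.

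**Working it through.** **Step 1: which contrast do the stated sizes belong to?** Inputs from Sample Size Estimation: two-sided α = .05, β = .10, 1:1 allocation, 70% referral. With unpooled variance, n per group = (1.960 + 1.282)² × [p₁(1−p₁) + p₂(1−p₂)] / (p₂−p₁)², divided by 0.70.

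- DR, 10% vs 15%: 914.1 / 0.70 = 1306 (stated 1306).
- AMD, 5% vs 10%: 577.9 / 0.70 = 825.6 (stated 825).

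Both sizes are reproduced as disease-specific calculations.

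**Step 2: what would the literal definition test on the same participants?** Assumptions not in the document:

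- the number eligible for both diseases, o, is 0, 400 or 825 per arm (825 is the extreme in which everyone in the AMD group also has diabetes);
- the diseases are independent within a person;
- confirmed rates are 100% or 70% of the stated rates, the latter counting non-attenders as non-cases.

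Participants per arm: N = 1306 + 825 − o, so 2131 down to 1306.

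Pooled rate = (1306·d + 825·a − o·d·a) / N, where d and a are the confirmed DR and AMD rates.

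Power = Φ{ [|p₂−p₁| − 1.96√(2p̄(1−p̄)/n)] / √([p₁(1−p₁)+p₂(1−p₂)]/n) }.

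Example (AMD-only effect, o = 0, 70% confirmation):

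- Control arm: (1306×0.07 + 825×0.035)/2131 = 120.3/2131 = 5.65%.
- AI arm: (1306×0.07 + 825×0.07)/2131 = 149.2/2131 = 7.00%.
- Pooled power: 44%. AMD-specific test on 825 per arm, 3.5% vs 7.0%: 89%.

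**Step 3: results over the assumed overlap.**

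| Scenario | Confirmation | Disease-specific power | Pooled power |
|---|---|---|---|
| AMD 5→10%, DR flat at 10% | 100% | AMD 97% | 55-60% |
| AMD 5→10%, DR flat at 10% | 70% | AMD 89% | 42-44% |
| DR 10→15%, AMD flat at 5% | 100% | DR 97% | about 93% |
| DR 10→15%, AMD flat at 5% | 70% | DR 89% | 80-81% |
| Both as planned | 100% | 97% each | over 99% |
| Both as planned | 70% | 89% each | about 99% |

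**Step 4: how often do the tests disagree within one trial?** From a simulation of 40,000 replicates under the same assumptions, giving the 100% then the 70% confirmation case:

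- AMD-only effect: the pooled test misses while a disease-specific test succeeds in 38-43%, then 46-49%.
- DR-only effect: the pooled test is positive while AMD is not significant in about 90%, then about 78%.
- Both as planned: both disease-specific tests succeed in 95%, then 80%. The pooled test is positive without both of them in about 5%, then 19-20%.

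At full rates, the planned pooled contrast is about 8.1% vs 13.1% (no overlap) to 12.8% vs 20.4% (overlap 825). Neither is a contrast that the protocol sizes.

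**The case against.** The strongest reply is that the governing rule is already there. The Randomization section calls for independent analyses by eligibility and lets dually eligible people enter both, which makes sense only with two denominators. No section calls the outcome composite or pooled, sizes such a test or prescribes one. Eligibility is described by disease, so the formula could be one template used twice, with DR or AMD meaning each in turn. This stands as evidence of intent. It does not repair the definition, whose denominator is everyone screened, with no restriction by eligibility, in both the abstract and the Primary Outcome section.

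Some stronger readings are tempting but not supported:

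- *The trial has two competing primary tests.* A reader might infer this, but only one analysis is prescribed. The other follows only from taking the definition literally.
- *The DR rate will be diluted by people without diabetes, and the AMD rate by people under 50.* That puts a one-disease numerator over the all-screened denominator. It is a third quantity, neither the pooled outcome nor the analysis in the Randomization section.
- *Every PPV statement is pooled.* The PPV prose in the Primary Outcome section names no disease. The pooling comes from the formula and the abstract.
- *The sample sizes are wrong.* They are reproduced and suit the disease-specific analyses.

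It is also fair to say that the power figures are conditional on a pooled test being run, and that under the planned effects the conflict is mild.

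**Conclusion.** The concern holds as an internal contradiction. The section that fixes the primary endpoint states a numerator and denominator that do not match the analysis rule or the powered contrasts. The disease-specific analysis is very probably what is meant.

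The consequence is conditional. It matters if someone follows the written definition and the two tools perform differently: roughly 42-60% pooled power against 89-97% for a real AMD-only effect, and a pooled positive in about 80-93% of trials for a DR-only effect. If both tools work as planned, pooled power is about 99% or more. These ranges rest on the protocol's rates and group sizes, the assumed overlap and independence, and 70-100% confirmation. The document does not state the share of dually eligible participants.

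This is not an omission that an analysis plan would fill. The definition is stated explicitly, and whoever writes the analysis plan could follow either section.

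**What to change.** In the abstract and the Primary Outcome section, replace the combined definitions with:

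- **DR detection rate:** confirmed DR among all randomised participants eligible for DR screening.
- **AMD detection rate:** confirmed AMD among all randomised participants eligible for AMD screening.
- **PPV, for each disease:** confirmed cases of that disease among eligible participants who screened positive for that disease and have a confirmatory assessment.

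State that any combined DR or AMD rate is descriptive and supports no claim for either disease.

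The cost is small. The sizes of 1306 and 825 per group stand, and no extra participants or visits are needed. The one practical demand is that the physician's screening call be recorded by disease in both arms. The AI output is already given by disease, and REDCap already records physician interpretation. The article describes randomisation as following the pilot, so the wording should be settled before randomisation starts.

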### Screening Workflow

Eligible outpatient participants will be invited to participate in the study during routine clinic visits. After providing written informed consent, participants will undergo color fundus photography as part of the screening procedure.

For participants with fundus images, screening findings will be reviewed by the general medicine physicians. Participants without suspected retinal abnormalities will be advised to undergo routine follow-up according to standard clinical practice, whereas participants with suspected retinal abnormalities will be referred to ophthalmology for confirmatory evaluation. Ophthalmologic diagnoses will be established by ophthalmologists, and these will serve as the gold standard for determining true disease status and for calculating the detection rate and positive predictive value (PPV) of DR and AMD screening. Referral completion and diagnostic outcomes will be recorded, including cases in which referred participants did not attend the ophthalmology visit. Outcomes will be classified as confirmed or nonconfirmed retinal disease based on ophthalmologic assessment.

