### Referral After a Positive Test

The examination will be repeated for images that are of insufficient quality for clinical interpretation. Across both groups, ophthalmology referral will be provided for participants with DR of stages 2 to 4 or AMD of stages 3 to 4, whereas participants not meeting these severity thresholds will be advised to undergo regular annual follow-up examinations. Confirmatory diagnosis of DR and AMD will follow the Early Treatment Diabetic Retinopathy Study [16], AREDS scales [23], and Beckman Initiative Classification [23] (Textbox 1). At 8 weeks after screening, referral completion and diagnostic outcomes will be assessed through review of electronic medical records, hospital visit records, and, when necessary, telephone follow-up.

Textbox 1.Confirmatory diagnosis of diabetic retinopathy (DR) and age-related macular degeneration (AMD).Diabetic retinopathyAccording to the Early Treatment Diabetic Retinopathy Study severity scale [24], primarily diagnosed through fundus photography and indirect ophthalmoscopy to identify typical features such as microaneurysms, retinal hemorrhages, hard exudates, and cotton-wool spots (soft exudates).Fluorescein angiography is generally not used as a primary diagnostic tool; however, it may be used in the evaluation of macular ischemia, edema, or neovascularization to inform treatment strategies. It facilitates the verification of the location and extent of lesions.The severity of DR is categorized into 5 stages: no diabetic retinopathy (no DR, stage 0), mild nonproliferative diabetic retinopathy (NPDR; stage 1), moderate NPDR (stage 2), severe NPDR (stage 3), and proliferative diabetic retinopathy (PDR; stage 4).Age-related macular degeneration:According to the Age-Related Eye Disease Study severity scale [25], fundus photography and indirect ophthalmoscopy are primarily used to identify the location, size, and number of drusen.On the basis of the Beckman Initiative Classification [23], AMD is classified into 4 severity levels based on drusen size and pigmentary abnormalities: no AMD (stage 1), early AMD (stage 2), intermediate AMD (stage 3), and advanced AMD (stage 4).When necessary, fluorescein angiography and optical coherence tomography are used to detect the choroidal neovascularization associated with AMD, the presence of macular edema, and retinal pigment epithelium abnormalities.

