### Limitations

Although this study is designed as a low-risk pragmatic clinical trial, several limitations should be acknowledged. First, while detection rate and PPV provide meaningful indicators of real-world screening effectiveness and downstream care engagement, they do not capture all dimensions of screening accuracy or long-term patient benefit. Important outcomes such as false-negative rates, disease progression, visual outcomes, and treatment-related outcomes are not designated as central end points in this protocol. These outcomes represent important areas for future investigation beyond the scope of the current pragmatic trial. Nonetheless, these will be estimated using the simulation models. Second, follow-up data may be incomplete for participants who seek subsequent ophthalmologic care outside the NTUH health care system, Fu Jen Catholic University Hospital, and Min-Sheng General Hospital. In such cases, confirmatory diagnostic results and downstream clinical outcomes may not be fully captured, potentially limiting the completeness of outcome assessment. This issue will be evaluated in the subgroup analyses. Third, the AI-assisted screening tools evaluated in this study are designed to detect specific retinal conditions only, including the DR and AMD. Other ocular diseases or retinal pathologies are not within the diagnostic scope of these tools and therefore may not be identified through the AI screening process while they may be identified by physicians. These will be evaluated in the post hoc analyses. Fourth, suboptimal image quality and inherent limitations in AI-based interpretation may result in false-positive or false-negative screening results, which could lead to unnecessary referrals or missed cases. To reduce this risk, image quality will be monitored at the time of acquisition, with repeat imaging performed when necessary, and cases with uncertain findings will still be referred for ophthalmologic evaluation. The impact will be evaluated in the subgroup or post hoc analyses. Fifth, real-world health care system constraints may influence the effectiveness of the screening-to-referral pathway. Limited ophthalmology workforce capacity and outpatient clinic availability may affect referral completion and time to confirmatory diagnosis, particularly in high-volume clinical settings. These constraints reflect routine clinical practice and may impact the generalizability of study findings to health care systems with different resource availability. Finally, it is important to emphasize that the AI-assisted screening tools are intended to support, rather than replace, clinical judgment. Treating physicians and ophthalmologists retain full responsibility for diagnostic confirmation and treatment decisions. Medical personnel involved in the study will receive training on appropriate interpretation and use of AI-assisted outputs to ensure safe and effective integration into clinical care.

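### Neither primary numerator states a disease stage, while referral and the DR sample size use moderate or worse disease, so over-called mild cases can count as successes

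*Protocol article*

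**What the plan says.** **Primary outcomes.** Under Primary Outcome, the detection rate is "the proportion of screened participants who receive a confirmatory diagnosis of DR or AMD" among all who undergo screening, and the PPV is "the proportion of participants with a confirmatory diagnosis among those who test positive in the screening". Neither the wording nor the two formulas name a stage. Screening Workflow makes the outcome binary: "Outcomes will be classified as confirmed or nonconfirmed retinal disease based on ophthalmologic assessment".

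**Confirmatory scales.** Textbox 1 grades DR from 0 to 4, with stage 1 being mild NPDR. It grades AMD from 1 to 4, with stage 1 meaning no AMD and stage 2 early AMD.

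**Referral.** Referral After a Positive Test says that "ophthalmology referral will be provided for participants with DR of stages 2 to 4 or AMD of stages 3 to 4". Screening Workflow is broader: "participants with suspected retinal abnormalities will be referred to ophthalmology for confirmatory evaluation". Limitations adds that "cases with uncertain findings will still be referred for ophthalmologic evaluation".

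**Sample size.** Sample Size Estimation quotes 27% for DR of any stage. It then sizes the DR comparison on 10% of patients with diabetes who "are diagnosed with clinically significant DR (stages 2 to 4"), rising to 15% with AI. The AMD comparison is sized on 5% rising to 10%, with no stage attached.

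**Eligibility.** The only exclusions are these: "Participants will be excluded if they decline participation or are unable to provide informed consent because of cognitive or communication limitations". Previously diagnosed DR or AMD is not mentioned.

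**The concern.** The protocol works with two targets. Referral and the DR sample size concern moderate or worse disease. The primary numerators, as written, concern any disease that an ophthalmologist confirms.

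The referral threshold does not remove the difference, because it acts on the screener's reading and not on the confirmed stage. A patient read as stage 2 and found at the ophthalmology visit to be stage 1 was referred in error under the threshold. That patient nevertheless has confirmed DR, and so enters the numerator of both primary outcomes.

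A PPV ought to penalise loose referral. With an any-stage numerator, over-calling mild disease is penalised only when the eye turns out to have no disease at all, so the two primary outcomes are weaker checks on each other. The trial is also open-label, and Study Design says the confirming ophthalmologists are not blinded. At stake is whether a positive result would mean that more referable disease was found, which is the question the DR comparison was sized to answer.

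**Working it through.** **1. The plan's own sample sizes.** Two proportions, unpooled variance, two-sided α = 0.05, power 90%, so (1.960 + 1.2816)² = 10.507; the result is divided by the assumed 70% referral.

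- DR: (0.10×0.90 + 0.15×0.85) × 10.507 / 0.05² = 914.1; 914.1 / 0.70 = 1306 per group, as stated (2612 in total).
- AMD: (0.05×0.95 + 0.10×0.90) × 10.507 / 0.05² = 577.9; 577.9 / 0.70 = 825.6, stated as 825 (1650 in total).

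The arithmetic reproduces. The DR figure belongs to stages 2-4. The AMD figure cannot be tied to any stage.

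**2. Effect of differential over-calling on the detection rate.** Inputs:

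- Referable DR 10% and attendance 70%, both from Sample Size Estimation.
- Mild DR 27% − 10% = 17%, by subtraction (assumed to apply in these clinics).
- All stage 2-4 disease flagged in both arms, so it contributes 0.70 × 0.10 = 7.0% to each (assumed).
- Share of mild cases over-called: 10% in the control arm, varied in the AI arm (assumed).

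Detection rate = 0.07 + 0.70 × 0.17 × (share over-called). Control arm: 0.07 + 0.119 × 0.10 = 8.19%.

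| Mild cases over-called, AI arm | Detection, AI arm | Difference from control | Chance of a significant result favouring AI, 1306 per group |
|---|---|---|---|
| 10% | 8.19% | 0 | 2.5% (nominal) |
| 20% | 9.38% | 1.19 points | 19% |
| 30% | 10.57% | 2.38 points | 55% |
| 40% | 11.76% | 3.57 points | 86% |
| 50% | 12.95% | 4.76 points | 98% |

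Detection of stages 2-4 is identical in every row. For scale, the planned difference after 70% attendance is 0.70 × (15% − 10%) = 3.5 points.

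**3. Effect on the PPV.** Keep all referable cases flagged (10%) and assume 5% false positives among the 73% without DR (0.05 × 0.73 = 3.65%).

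- 10% of mild cases over-called: flagged = 10 + 1.7 + 3.65 = 15.35%. PPV for stages 2-4 = 10 / 15.35 = 65%; PPV as written = 11.7 / 15.35 = 76%.
- 40% of mild cases over-called: flagged = 10 + 6.8 + 3.65 = 20.45%. PPV for stages 2-4 = 10 / 20.45 = 49%; PPV as written = 16.8 / 20.45 = 82%.

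Here the stage-specific PPV falls while the PPV as written rises. Step 1 of the objection shows inputs for which the PPV as written falls.

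**4. Sample size under each numerator.** Restricted to stages 2-4, DR stays at 2612. If any-stage DR were intended, with 27% taken as the control rate and a 5-point gain (both assumed), the same formula gives (0.27×0.73 + 0.32×0.68) × 10.507 / 0.05² = 1743; 1743 / 0.70 = 2490 per group. The planned 1306 per group (914 after 70%) would then have about 65% power.

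**The case against.** 1. **The looser arm need not win on both outcomes.** This is correct. An extra referral raises the PPV only if its chance of confirmation exceeds the arm's current PPV. Take 10% prevalence and the published AI sensitivity of 92.2% and specificity of 89.5%, and assume half of the false positives are mild. The PPV as written is (9.22 + 4.725) / 18.67 = 74.7%. An assumed stricter control arm (sensitivity 61.5%, specificity 95%, same mild share) has (6.15 + 2.25) / 10.65 = 78.9%. The looser arm then has the lower PPV, so the claim is limited to sometimes.

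2. **Over-calling can occur in either arm.** Also correct. Physicians, not the software, decide on referral, and the documents do not show that the AI arm will over-call mild disease more. The bias depends on the difference between arms and could run either way.

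3. **The protocol may intend referable disease.** The confirmatory diagnosis is described directly after the referral threshold, the AMD software output is split at level 3, and the DR sample size names stages 2-4. That is a fair guess at intent, but the outcome definition does not say it, and the binary confirmed or nonconfirmed classification points the other way.

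4. **Two stronger readings are tempting.** A reader might infer that the AMD sample size also rests on stages 3-4; the document attaches no stage to the 5% and 10%. A reader might also infer that previously known disease is counted as detected through record review. Eligibility does not exclude such people, but no section says that earlier diagnoses count: Screening Workflow rests outcomes on ophthalmologic assessment, and the 8-week record review concerns referral completion and diagnostic outcomes. The share of known disease is not given.

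**Conclusion.** The point holds as a mismatch within the protocol. Both primary numerators lack a severity threshold, while the stated referral threshold is DR 2-4 or AMD 3-4 and the DR comparison is sized on stages 2-4. Followed literally, over-called mild disease that is confirmed counts as success in both primary outcomes. This is a flaw in the rule as stated and not just detail left to another document.

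The size depends on how differently the arms over-call. Under the assumptions shown, 10% versus 30-50% of mild cases gives 8.2% versus 10.6-13.0% and a 55-98% chance of a significant result with no gain in referable disease. With equal over-calling there is no such bias. The 17% mild share comes from subtracting the protocol's own figures; the over-calling shares and equal referable detection are assumed. The documents do not support saying that the AI arm will benefit, or that the looser arm always wins on both outcomes. Known disease supports a supplementary analysis and no more.

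**What to change.** - Define the numerators of detection rate and PPV as ophthalmologist-confirmed disease at the stage the trial is sized for. For DR this is stages 2-4, which leaves the sample size at 2612.
- For AMD, state the stage to which the 5% and 10% refer, and use that stage in both numerators.
- Report any-stage detection as a secondary outcome.
- Reconcile Screening Workflow, Referral After a Positive Test, Primary Outcome and Sample Size Estimation, including the differing descriptions of who is referred. Which referral rule applies is for the investigators to decide.
- Record prior diagnoses of DR and AMD at baseline, and add an analysis restricted to new diagnoses.

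The cost is mostly wording, since stages are already graded under Textbox 1, plus one baseline record check. Headline detection rates and PPV will be lower than with an any-stage numerator. The non-randomised pilot phase gives room to make the change before randomisation starts.
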